**Methods:**

A school-based clustered randomised controlled trial (cRCT) design with 12 months of follow-up. **Subjects:** At least 408 secondary school students who attend the 3rd year of E.S.O (Compulsory secondary education for 13- to 14-year- olds) will be recruited from 8 schools within Barcelona city, Catalonia (Spain). **Intervention:** A dose-response intervention will be delivered with 4 arms: 1) Sensitivity Programme (SP) in Mental Health (1 h); 2) Mental Health Literacy (MHL) Programme (6 h); 3) MHL plus first-person Stigma Reduction (MHL + SR) (7 h); 4) Control group: waiting list.

**Primary outcomes:** 1) MHL: EspaiJove.net MHL Test (EMHLT); 2) Stigma: Reported and Intended Behaviour Scale (RIBS) and Community Attitudes toward the Mentally Ill (CAMI). **Others outcomes:** 1) Acceptability of intervention; 2) Mental health symptoms and emotional well-being (SDQ); 3) States of Change Scale (SCS); 4) Bullying and Cyberbullying; 5) Quality of life (EQ-5D); 6) Help seeking and use of treatment; 7) Health benefits.

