## Methods

### Study design

The study is a multicentre and school-based clustered randomised controlled trial (cRCT) with four intervention arms. Eligible schools are randomly allocated either to an intervention group or a control group (see Fig. 1). Data will be collected at baseline, and at 2 weeks, 6 months and 12 months following the intervention. Each school will participate in the study for two academic years from September 2017 to September 2019.

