### Recruitment process

The recruitment process for the trial began in September 2016. All eligible secondary schools within Barcelona city are contacted and encouraged to participate in the study. Emails providing information about the study are sent to all schools, and among those schools that had shown an interest in participating, a presentation is delivered at the school by two project researchers. Once a school agreed to participate, consent letters are sent out to the parents of all participating students.

Out of all the schools that accept participation in the study, a cluster randomisation by school and individual students as participants is conducted. The total sample estimated within a minimum of 408 adolescents will be divided into three experimental groups and one control waiting list. The randomisation assignment will be carried out through a computer program, and the group assignment will be 1:1:1:1.Each interviewer blinded the assessments.

Pre-treatment questionnaires will be completed approximately 2 weeks before the intervention by all students (intervention and control groups). A code will be used to match participant answers over time whilst preserving anonymity. One teacher will be the unique person responsible for keeping the identification number and corresponding student. Two researchers will be responsible for supplying each student with a questionnaire for its completion during each assessment within the study. The class teacher will be present in the classroom during the questionnaire administration involved in the data collection with the aim of minimising missing data and errors when providing the questionnaires.

A second evaluation will be performed approximately 2 weeks after the intervention. A third and fourth evaluation will be examined at 6 and 12 months, respectively. Table 2 shows the data collection and intervention programme timelines.

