### Statistical analysis

To analyse the effectiveness of the EspaiJove.net intervention, an experimental design will be created to evaluate the programme, randomised by clusters (schools) and with a control group on the waiting list. The statistical analyses to be performed will be as follows. A description of the sociodemographic variables of the sample at baseline will be done through a univariate analysis of the selected variables from the total sample and stratified by type of intervention. Then, to evaluate the effectiveness of all programmes and to achieve statistical significance for all outcomes after the intervention, an unadjusted bivariate primary analysis will be performed. Data scores after the intervention will be analysed with ANOVA, assuming that the baseline data will be similar due to the randomisation process across groups. Finally, a multivariate and adjusted analysis, as necessary, will be employed to evaluate the effectiveness of those programmes so as to achieve statistical significance after the intervention. Data will be analysed with Generalised Equation Estimates (GEE) to assess the efficacy of the intervention. This statistical model is appropriate for longitudinal clustering analyses since this study design (schools) will allow us to consider the individual data correlation within the same cluster group. Analyses will be based on an intention-to-treat analysis.

We will also examine relative and absolute risk reduction, (RRR) and (ARR), respectively. Additionally, to analyse the acceptability and satisfaction of each programme, a descriptive analysis will be performed to observe the percentage of acceptability and satisfaction. Statistical analyses will be performed using the SPSS [48].

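### The analysis labelled primary omits baseline on an assumption of similar arms that about 2 schools per arm cannot support, although every primary outcome is measured at baseline

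*Protocol article*

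**What the plan says.** Under Statistical analysis, the protocol article says that, for all outcomes, "an unadjusted bivariate primary analysis will be performed". It then gives the method, an ANOVA of post-intervention scores, and its justification: "assuming that the baseline data will be similar due to the randomisation process across groups".

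Two further steps follow. One is conditional and names no covariates: "Finally, a multivariate and adjusted analysis, as necessary, will be employed". The other is a model for correlated data: "Data will be analysed with Generalised Equation Estimates (GEE) to assess the efficacy of the intervention". The article justifies the GEE by the correlation of pupils within schools and does not say whether the baseline score enters it.

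On the design, the Study design section says: "Eligible schools are randomly allocated either to an intervention group or a control group". According to the abstract, pupils "will be recruited from 8 schools within Barcelona city". The Recruitment process section gives 1:1:1:1 allocation to four arms. The Sample section mentions strata by number of classes, in wording that is hard to interpret. It mentions no stratification by school type, district or baseline score.

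Table 3 marks the literacy questionnaire, RIBS and the CAMI Authoritarianism subscale at pre-intervention. The Recruitment process section has students in all groups complete the questionnaires about two weeks before the intervention.

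**The concern.** Randomisation makes arms comparable on average over many possible allocations. It makes them similar in one allocation only when many units are randomised. Here the units are 8 schools, drawn from public and private schools in several districts, so two arms can easily start some way apart. The plan gives similarity as its reason for leaving baseline out of the analysis it calls primary.

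Two things are at stake. The estimated contrasts may partly reflect where the schools started. And precision that could be had from data already being collected is given up.

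**Working it through.** **Inputs from the protocol article.** 8 schools; four arms at 1:1:1:1; 408 students; effect size 0.18, alpha 0.05, power 80%, 85 per group (340).

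**Assumed, not in the document.** ICC 0.01 to 0.10; pupil-level baseline-to-outcome correlation r_p = 0.5; school-level correlation r_s = 0.5 to 0.8; the same ICC and unit variance at baseline and follow-up.

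**1. The plan's own figure.** For a one-way ANOVA with 4 groups and noncentrality N × f² = 340 × 0.18² = 11.0, power is 0.799. The smallest balanced N reaching 0.80 is 344. So 340 reproduces closely when 0.18 is read as Cohen's f. Read as a standardised difference between two means, 0.18 would need 485 per arm.

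**2. Target spread on the SD scale.** f = 0.18 means that the SD of the four arm means is 0.18.
- Two arms high and two low: spread = 2 × 0.18 = 0.36 SD.
- Two extreme arms and two in the middle: spread = 2√2 × 0.18 = 0.51 SD.

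**3. Clusters.** 8/4 = 2 schools per arm; 408/8 = 51 pupils per school; 102 pupils per arm.

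**4. Chance baseline differences.** Design effect DE = 1 + 50 × ICC. SD of the difference between two arms = √(2 × DE/102). Expected spread of four arm means = 2.06 × √(DE/102).

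| ICC | DE | SD of two-arm difference | Chance that it exceeds 0.25 SD | Expected four-arm spread |
|---|---|---|---|---|
| 0 (individual randomisation) | 1.0 | 0.14 | 7% | 0.20 |
| 0.01 | 1.5 | 0.17 | 14.5% | 0.25 |
| 0.02 | 2.0 | 0.20 | 21% | 0.29 |
| 0.05 | 3.5 | 0.26 | 34% | 0.38 |
| 0.10 | 6.0 | 0.34 | 47% | 0.50 |

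**5. Share of a baseline gap that carries into the post-intervention contrast.** Share = [ICC × r_s + (1 − ICC) × r_p/51] / [ICC + (1 − ICC)/51].
- r_s = 0.5: share = 0.50 at any ICC.
- r_s = 0.8, ICC 0.05: (0.0400 + 0.0093)/0.0686 = 0.72.

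The carried spread therefore runs from 0.29 × 0.50 = 0.14 SD (ICC 0.02) to 0.38 × 0.72 = 0.27 SD (ICC 0.05), against the target of 0.36 to 0.51 SD.

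**6. Precision given up.** With the individual baseline score as covariate and slope 0.5, the variance ratio (adjusted to unadjusted) is [ICC × (1 − 2 × 0.5 × r_s + 0.25) + (1 − ICC) × 0.75/51] / [ICC + (1 − ICC)/51].
- r_s = 0.5: ratio 0.75.
- r_s = 0.8, ICC 0.05: (0.0225 + 0.0140)/0.0686 = 0.53.

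That is a reduction of 25% to 47%. Simulation of the same settings gave 24% to 46%.

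**The case against.** **The plan does not stop at the ANOVA.** A reader might infer that post-intervention scores are all that is ever analysed. The documents do not support that: an adjusted analysis and a GEE follow, and a longitudinal GEE over the Table 3 time points may well use baseline. A full covariate list is also something an article may leave to an analysis plan. This stands, but it does not remove the point. The adjusted analysis is conditional, the GEE states no baseline term, and the label of primary and the similarity assumption are choices the article makes expressly.

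**Randomisation makes the comparison unbiased.** True over allocations. A reader might infer that the plan is biased, or that a baseline gap passes in full into the estimate. Neither follows. The gap carries over only in proportion to the baseline-outcome association, about 0.50 to 0.72 under the assumptions used, and the expected carried spread is below the target spread. If the analysis respects clustering, its standard error already allows for chance differences between schools.

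**Validity is a clustering matter.** Also true. A pupil-level ANOVA with 2 schools per arm has a simulated type I error of about 16%, 28% and 53% at ICC 0.01, 0.02 and 0.05, with 51 pupils per school. That is a separate defect, and baseline adjustment alone does not cure it.

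**Two schools per arm is derived, not stated.** The stratification wording in the Sample section is ambiguous. But Study design allocates schools, the Intervention section speaks of control schools, and Statistical analysis names schools as the clusters.

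**Conclusion.** The point holds as a matter of efficiency and of accuracy in the realised allocation, and it should be fixed. The stated reason for omitting baseline is not sound for this design: at assumed ICCs of 0.02 to 0.10, two given arms would differ at baseline by more than 0.25 SD with a chance of 21% to 47%, against 7% under individual randomisation. The chance spread expected to reach the outcome, 0.14 to 0.27 SD at ICC 0.02 to 0.05, is material beside the effect the trial is sized for.

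The size depends on an ICC and on correlations that the document does not give, and on about 2 schools per arm. It does not show that the trial's estimates are biased or that the plan ignores baseline throughout.

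**What to change.** Delete the similarity assumption. Make the school-clustered model the primary analysis and prespecify each outcome's own individual baseline score as a covariate in it. Drop the conditional wording for this covariate, so that its inclusion cannot depend on the data. The covariate must sit in the clustered model; adding it to the pupil-level ANOVA would leave the clustering problem untouched.

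The change needs no extra data, since all three primary instruments are already scheduled at baseline. An individual-level covariate uses none of the 8 − 4 = 4 school-level degrees of freedom. The cost is a change of wording, to be made before outcome data are analysed.

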**Table 2 Tab2:**
[figure not shown]
Data collection and intervention programme timeline

An Informed Consent Form (for children and parents) will be required for all participants prior to their involvement in the study. The confidentiality of the participants (children) will be protected using an encryption key for any personal details within the data (school 1–8, class 1–6, identification number 1–34). The key will be stored separately. Ethical approval was granted by the Fundació Unió Catalana Hospitals.

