## Discussion

The aim of this paper is to describe the cRCT regarding a universal mental health literacy intervention called “EspaiJove.net” designed to promote mental health knowledge, increase help-seeking, reduce the stigma associated with mental illness, and prevent mental disorders in Spanish school settings.

Among the interventions to promote mental health and prevent mental disorders, MHL has played an important role, given that it helps young people to recognise, manage and seek appropriate help when a mental disorder develops, and it can also reduce the stigma associated with mental health.

The *EspaiJove.net* has the potential to provide a valid, new and useful school-based intervention for adolescents in Spanish settings aimed at preventing mental disorders. The contents of the intervention include useful knowledge about mental health, such as definitions of mental health and mental disorders, recognition of mental disorders, healthy behaviours and risk behaviours and bullying/cyber-bullying behaviours, as well as information about the most prevalent mental disorders during adolescence. Furthermore, this study assesses the magnitude of the stigma associated with a delay in help-seeking and the use of treatment.

Some limitations of the study protocol could be as follows. Firstly, the possible loss of missing subjects during the follow-up where there may be a possible decrease in the statistical power and selection bias. These will be minimised with successive reminders to schools, tutors/teachers, and students. Additionally, school settings promote higher retention rates of participants. The intention-to-treat imputation method will be used to analyse the missing subjects, and socio-demographic comparison analyses will be performed among missing and included subjects to search for group differences. Secondly, the selection of the study sample is limited to Barcelona city which may affect the generalisation of the results among the rest of the Spanish population.

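### GEE with 8 schools in four arms (about two per arm) does not hold its 5% error rate on standard large-sample inference; arm comparisons need a reference distribution on the between-school degrees of freedom

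*Protocol article*

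**What the plan says.** Under Statistical analysis, the protocol article describes a design "randomised by clusters (schools) and with a control group on the waiting list". It plans an unadjusted ANOVA first and then an adjusted analysis: "Data will be analysed with Generalised Equation Estimates (GEE) to assess the efficacy of the intervention". It calls this model appropriate because it takes account of correlation within a school, and it names SPSS as the software. It does not name a variance estimator, a reference distribution or degrees of freedom.

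The number of clusters follows from other sections:
- Abstract, Methods: pupils "will be recruited from 8 schools within Barcelona city".
- Recruitment process, in the coding scheme after Table 2: "school 1–8, class 1–6, identification number 1–34".
- Study design: a "clustered randomised controlled trial (cRCT) with four intervention arms".
- Recruitment process: "the group assignment will be 1:1:1:1".

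The limitations in the Discussion cover loss to follow-up and restriction to one city. The number of schools is not among them.

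**The concern.** The ANOVA treats pupils as independent, so GEE is the only planned analysis that allows for schools. Its usual standard errors and Wald tests are justified as the number of clusters grows, and each arm has about two. The spread between schools within an arm then rests on a single difference between two school means, yet a z or chi-square reference treats that spread as known.

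If this inference is used, intervals are too narrow and an ineffective programme can easily look effective. The Discussion says the programme will be implemented in other Barcelona schools if it proves effective, so a false positive has a practical consequence.

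**Working it through.** **Inputs.** From the article: 8 schools, 4 arms, 1:1:1:1 allocation, alpha 0.05, 408 pupils. Derived: 8/4 = 2 schools per arm and 408/8 = 51 pupils per school. Assumed: equal school sizes, one outcome at one visit, and ICCs of 0.02 and 0.05, because the article gives none.

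**The plan's own figure.** A four-group one-way ANOVA with f = 0.18 and N = 340 has noncentrality 340 × 0.18² = 11.02 and power 0.799. The stated 85 per group therefore reproduces to within rounding (the strict solution is 86). It is a pupil-level figure, and the number of schools does not enter it. The article gives no error rate or standard error for the GEE to reproduce.

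**Closed form, one arm against control, uncorrected sandwich.** Let σ² be the variance of a school mean.
- True variance of the difference between two arm means: σ²/2 + σ²/2 = σ².
- Sandwich variance: SS/4, where SS is the sum of squared deviations of the four school means from their own arm means, distributed as σ²χ² on 2 df. Its expectation is 2σ²/4 = σ²/2, half the truth.
- Wald statistic: Z/√(χ²₂/4) = √2 × t on 2 df.
- Type I error: P(|t₂| > 1.96/√2 = 1.386). Since P(|t₂| > c) = 1 − c/√(c² + 2), this is 1 − 1.386/1.980 = **30.0%**.

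σ² cancels, so with equal school sizes the result does not depend on the ICC.

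**Simulated school means (400,000 null trials).**

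| Quantity, uncorrected sandwich | Result |
|---|---|
| One arm vs control, z reference | 29.9% |
| At least one of three arms vs control | 57% |
| Joint 3-df Wald, chi-square reference | 63% |
| Mean variance / true variance | 0.50 |
| Median standard error / true standard error | 0.59 |

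**Full GEE fits to 8 × 51 pupils (400 null trials per setting).**

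| ICC, working correlation | Robust, pairwise | Robust, joint | Model-based, pairwise |
|---|---|---|---|
| 0.02, independence | 29.3% | 60.5% | 15.3% |
| 0.02, exchangeable | 27.8% | 62.3% | 20.8% |
| 0.05, independence | 28.5% | 65.0% | 27.3% |
| 0.05, exchangeable | 25.3% | 61.3% | 20.8% |

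With 400 trials, the Monte Carlo standard error near 30% is √(0.3 × 0.7/400) = 2.3 points, so these fits broadly agree with the closed form.

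**Candidate repairs, pairwise, two schools per arm.**

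| Variance and reference | Type I error |
|---|---|
| Doubled sandwich (unbiased here), z | P(\|t₂\| > 1.96) = 18.9% |
| Doubled sandwich, t on 4 df | P(\|t₂\| > 2.776) = 10.9% |
| Mancl-DeRouen (sandwich × 4 here), z | P(\|t₂\| > 1.96√2) = 10.9% |
| Mancl-DeRouen, t on 4 df | P(\|t₂\| > 2.776√2) = 5.9% |
| Doubled sandwich, t on 2 df | 5.0% |
| Between-school variance pooled over four arms, t on 4 df | 5.0% (4.9% simulated) |

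**Power once the test is valid.** For a school-level F test on (3, 4) df with f = 0.18 and 340 pupils (340/8 = 42.5 per school), the noncentrality is 11.02/[1 + 41.5 × ICC].
- ICC 0: noncentrality 11.02, power 39%.
- ICC 0.02: 11.02/1.83 = 6.02, power 23%.
- ICC 0.05: 11.02/3.075 = 3.58, power 16%.

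**The case against.** **The variance estimator is not stated.** A reader might infer that the trial relies on uncorrected robust standard errors. The article names only GEE and SPSS, and a correction could sit in an analysis plan that is not shown. That stands, so the 30% and 63% are conditional. What remains is what the article itself fixes: GEE called appropriate for 8 schools in four arms. Model-based standard errors fail as well, and an unbiased variance with a z reference still gives 18.9%.

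**Two schools per arm is derived.** The Sample section speaks of distributing schools by number of classes and of several randomisations within strata, which could be read as allocating classes. If so, and if identification numbers run within a class, 408/34 gives at least 12 classes, or 3 per arm. With three independent clusters per arm the uncorrected test still has 18.6% error, with four 14% and with ten 8%. Study design, Recruitment process and Statistical analysis all make the school the randomised unit, and the Intervention section refers to control schools. The wording lowers certainty but does not overturn the point.

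**GEE is not the primary analysis.** The article gives that place to the unadjusted ANOVA, and GEE follows as the adjusted analysis. This is correct. GEE still matters as the only planned analysis that allows for clustering.

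**Missing data.** It is tempting to add that GEE on observed data needs missingness completely at random. The Discussion says "The intention-to-treat imputation method will be used to analyse the missing subjects". The phrase is loose, but a plan that intends to impute is not a plan to analyse observed data only, and the choice of imputation method is ordinary analysis-plan detail. That complaint is not part of this point.

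**Conclusion.** The point holds in conditional form. With about two schools per arm, GEE with a z or chi-square reference is not a valid basis for the arm comparisons. With the uncorrected sandwich, true error at nominal 5% is about 30% per arm-versus-control test and about 63% for the joint test. With model-based standard errors the pairwise figure is about 15% to 27%.

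This assumes school as the randomised unit, two schools per arm of equal size, and a single outcome and visit. The robust figures do not depend on the ICC under those assumptions; the model-based range rests on assumed ICCs of 0.02 and 0.05. The documents do not show that the trial will use an uncorrected estimator. They do show a method called appropriate for a number of clusters at which its standard inference fails, with the number of schools missing from the limitations.

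**What to change.** 1. Base the arm comparisons on a baseline-adjusted school-level summary analysis, or on a linear mixed model with a random school effect. Refer them to t or F on the between-school degrees of freedom: 8 − 4 = 4, less one for each school-level covariate. Fix these degrees of freedom in advance.
2. If GEE is kept, name a bias-corrected variance and a matching reference distribution. For a pairwise contrast whose variance uses only the schools of its own two arms, that is t on 2 df. Bias correction with t on 4 df is not safe as a general rule, as the 10.9% above shows.
3. Add the small number of schools to the limitations in the Discussion, and state the resulting power.

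The change of method costs some analysis-plan wording and modest changes in software syntax. The real cost is precision: the critical value rises from 1.96 to 2.78 (4 df) or 4.30 (2 df), and power for the planned effect falls to about 39% at ICC 0, 23% at 0.02 and 16% at 0.05. A valid analysis restores the error rate; only more schools would restore power.
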